# The effect of extracorporeal shock wave therapy in acute traumatic spinal cord injury on motor and sensory function within 6 months post-injury: a study protocol for a two-arm three-stage adaptive, prospective, multi-center, randomized, blinded, placebo-controlled clinical trial

**DOI:** 10.1186/s13063-022-06161-8

**Published:** 2022-04-01

**Keywords:** Spinal cord injuries, Extracorporeal shock wave therapy, Off-label use, Treatment outcome

## Abstract

**Background:**

The pathological mechanism in acute spinal cord injury (SCI) is dual sequential: the primary mechanical lesion and the secondary injury due to a cascade of biochemical and pathological changes initiated by the primary lesion. Therapeutic approaches have focused on modulating the mechanisms of secondary injury. Despite extensive efforts in the treatment of SCI, there is yet no causal, curative treatment approach available.

Extracorporeal shock wave therapy (ESWT) has been successfully implemented in clinical use. Biological responses to therapeutic shock waves include altered metabolic activity of various cell types due to direct and indirect mechanotransduction leading to improved migration, proliferation, chemotaxis, modulation of the inflammatory response, angiogenesis, and neovascularization, thus inducing rather a regeneration than repair.

The aim of this clinical study is to investigate the effect of ESWT in humans within the first 48 h after an acute traumatic SCI, with the objective to intervene in the secondary injury phase in order to reduce the extent of neuronal loss.

**Methods:**

This two-arm three-stage adaptive, prospective, multi-center, randomized, blinded, placebo-controlled study has been initiated in July 2020, and a total of 82 patients with acute traumatic SCI will be recruited for the first stage in 15 participating hospitals as part of a two-armed three-stage adaptive trial design. The focused ESWT (energy flux density: 0.1–0.19 mJ/mm^2^, frequency: 2–5 Hz) is applied once at the level of the lesion, five segments above/below, and on the plantar surface of both feet within the first 48 h after trauma.

The degree of improvement in motor and sensory function after 6 months post-injury is the primary endpoint of the study. Secondary endpoints include routine blood chemistry parameters, the degree of spasticity, the ability to walk, urological function, quality of life, and the independence in everyday life.

**Discussion:**

The application of ESWT activates the nervous tissue regeneration involving a multitude of various biochemical and cellular events and leads to a decreased neuronal loss. ESWT might contribute to an improvement in the treatment of acute traumatic SCI in future clinical use.

**Trial registration:**

ClinicalTrials.gov
NCT04474106

**Supplementary Information:**

The online version contains supplementary material available at 10.1186/s13063-022-06161-8.

## Background

Spinal cord injury (SCI) results in devastating, lifelong effects on the health and quality of life of affected patients and high financial burdens on affected individuals, their families, and the health care system in general. Beyond the primary trauma of the spinal cord, secondary health complications lead to a considerable reduction in quality of life [1].

For traumatic spinal cord injury (tSCI), an estimated global annual incidence rate of 23 per million is reported [1, 2]. In Western Europe, there are around 16 people per year and one million people who suffer from a tSCI. Globally, the incidence as well as the prevalence of tSCI is low [2].

In developed and developing countries, men between the age of 18 and 32 are most affected by tSCI. In developed countries, due to an aging population, males and females above the age of 65 are affected by falls from low altitudes (1 m or less) [2]. Age at injury has increased from 28.7 years in the 1970s to 42.2 years during 2010 to 2014 in the USA [3]. Worldwide, the mean age of patients sustaining a tSCI is reported as 33 years [4].

The leading causes of tSCI are road traffic accidents, falls, and violence. Overall, road traffic collisions are the most common cause of tSCI [3, 5]. While transport is a significant cause of SCI in all age groups, falls are the most common cause over the age of 60 [5]. Although sports-related injuries account for only 8.7% of all SCI, they represent the second most frequent cause of tSCI in those under the age of 30 years [6, 7]. Literature reports that sports with high risk of sustaining SCI are diving, skiing, rugby, horseback riding, hockey, American football, and snowboarding [1, 7]. Cervical injury is by far the most predominant level of injury for hockey (81.5% cervical), skiing (81.1%), diving (98.2%), and American football (96.3%). Over half of injuries due to horseback riding and snowboarding accidents affect the thoracic or lumbosacral neurological level [1].

One-third of patients with SCI are reported to be tetraplegic and more than 50% presenting as AIS A grade (= a complete lesion) [4, 7]. The worldwide overall sex distribution (men/women) is reported to be 3.8/1 independent of injury cause and age [4]. The proportion of cervical injuries has increased over the last decades [8].

Improvements in diagnostics, pre-hospital management, fast transfer to specialized units, good shock management, the potential for early surgical decompression, and advanced medical rehabilitation methods result in higher life expectancy and lower mortality rates in high-income countries [5, 9]. Though, life expectancy after SCI is reduced compared to the general population. The mortality depends on the level and severity of the lesion and the availability of clinical care. Mortality is particularly high in the first year after injury [5].

Despite worldwide intensive efforts, SCI remains a devastating condition for which there is yet no causal treatment available [10].

### Pathophysiology

Based on imaging and histology of the injured human spinal cord, tSCI is classified as a “contusion with cavity formation,” “massive compression,” or “laceration” [10]. The primary injury mechanism involves the initial mechanical damage due to local deformation and energy transformation that occurs within the spinal cord at the moment of injury, which is irreversible [11]. This primary mechanical injury leads to a cascade of biological events, described as “secondary injury,” which occurs within minutes to weeks after the injury and further compromises neurological function [10].

Injuries to nervous tissue are followed by a rapid process of degenerative events called Wallerian degeneration in anterograde direction from the initial injury site [12, 13]. Wallerian degeneration as one of the initial pathological results of axotomy is considered an unavoidable consequence of SCI [14]. In the central and peripheral nervous system, the early phase of Wallerian degeneration includes the granular disintegration of the cytoskeleton, in which the cytoskeletal proteins of the axon are rapidly degraded to granular residues. This occurs between 18 and 48 h after injury and progresses away from the lesion site [13]. The proximal nerve stump retrograde from the initial lesion is also affected and chromatolysis reaches up to the first Ranvier node [12]. Numerous biochemical mechanisms that might explain the progressive post-traumatic damage of spinal cord tissue have been postulated: vascular changes including hemorrhage, vasospasm, thrombosis, loss of autoregulation, breakdown of blood-brain barrier, and infiltration of inflammatory cells leading to edema, necrosis, and ischemia; free radical formation and lipid peroxidation that cause oxidative death in spinal cord neurons; disruption of ionic balance; glutamate excitotoxicity; apoptosis; and an inflammatory response following the trauma. Subsuming, the secondary injury leads to neurological impairments in both anterograde and retrograde directions owing to white matter demyelination, gray matter dissolution, connective tissue deposition, and glial scar formation. The glial scar acts like a physical barrier, preventing axons to grow through it [10].

In addition to loss of sensory and motor function, central neuropathic pain in many cases is a consequence of SCI due to maladaptive synaptic circuits in the spinal dorsal horn that result in neuronal hyperexcitability. Pain transmission in the spinal dorsal horn is persistently increased due to neuronal hyperexcitability. These neurochemical and neuroanatomical changes often elicit chronic pain syndromes after SCI [15, 16].

It has been postulated that mechanisms of secondary injury are preventable and potentially reversible [9–11].

### Extracorporeal shock wave therapy (ESWT)

Shock waves are short-term acoustic pressure pulses that travel through tissue in a wave-like manner. Shock waves can be produced by electrohydraulic, electromagnetic, and piezo-electric sources. Extracorporeal shock wave therapy is subdivided into the categories “high-energy” (for bone tissue) and “low-energy” (for soft tissue) according to the energy flux density measured in mJ/mm^2^. Another classification is “focused” or “de-focused” depending on the reflector shape. Defocused shock wave applicators provide a larger diameter of the shock wave field and therefore enable the treatment of a larger tissue area. Focused shock waves allow for concentration of energy at one small therapeutic area of interest and are typically used for lithotripsy and to foster bone healing [12, 17].

The physical impact of shock waves including pressure, tensile, and shearing forces are translated to complex biochemical signals. This signaling process is called mechanotransduction. The underlying mechanism of mechanotransduction is that organ formation and tissue regeneration is the dynamic interaction between a cell and its microenvironment, including forces applied to them [12, 18].

Several biological responses to therapeutic shock waves have been postulated, including angiogenesis and neovascularization, anti-inflammatory and antimicrobial effects, the release of growth factors, the activation of mesenchymal stem cells, stimulated cell proliferation and differentiation, and suppression of nociception [12, 18–20].

ESWT has been clinically implemented in the treatment of chronic wounds, venous or diabetic ulcers, and ischemic heart disease and to stimulate and reactivate bone healing in non-healing fractures and the integration of skin grafts [12, 17, 19, 21].

In December 2018, STORZ MEDICAL has received the CE approval for transcranial pulse stimulation for the treatment of patients with Alzheimer’s disease. This technology allows a focused stimulation of the brain at a depth of up to 5 cm [22].

### Pre-clinical and clinical data on the effect of ESWT on nerve regeneration

Hausner and colleagues found significantly greater numbers of myelinated fibers in peripheral nerves after a one-time ESWT application in an experimental model on rats after a homotopic nerve autograft into the sciatic nerve [23]. Another study by Lobenwein et al. performed a spinal cord ischemia model in mice. ESWT was applied immediately after surgery and the treated animals showed a significantly better motor function and decreased neuronal degeneration compared to the control group within the first 7 days after surgery. In the same study, ESWT was applied to human spinal cord slices ex vivo 2 h post-mortem. They found significantly higher numbers of cells in the treatment group at 24 and 48 h ﻿after treatment compared to the control slices [24]. Furthermore, low-energy ESWT for the duration of 3 weeks on a spinal cord contusion injury model in rats resulted in significantly better locomotor improvement, reduced neuronal loss, an increased vascular endothelial growth factor (VEGF) expression in various neural cells, and an upregulation of brain-derived neurotrophic factor (BDNF) compared to the control animals [25–27].

Also, several other indications for ESWT had been evaluated: Lohse-Busch et al. conducted a study on the effect of focused transcranial ESWT in patients with unresponsive wakefulness syndrome (apallic syndrome). The ESWT was applied to the neurocranium three times a week for 4 weeks with an energy flow density between 0.2 and 0.3 mJ/mm^2^. An improvement of 135.9% in the German Coma Remission Scale (KRS) and 43.6% in the Glasgow Coma Scale (GCS) was observed after four to eight (average of 4.5) treatment series. No adverse effects and no triggering of epileptic seizures have been reported [28].

Davis et al. found significantly reduced inflammatory cell infiltrate of both neutrophils and macrophages in ESWT-treated burn wounds in a murine burn wound model 24 h following burn injury. ESWT was applied once 1 h after the burn injury and resulted in a significant downregulation of the expression of several acute-phase pro-inflammatory cytokines [29].

Additionally in vitro experiments showed that ESWT significantly enhanced the expression of the anti-inflammatory cytokine IL-10 when applied to human umbilical vein endothelial cells or monocyte-derived macrophages [30, 31]. Also, shock waves did not induce activation of resting macrophages at any energy level used [31].

Summarizing these results, several in vitro studies and animal trials reported that low-energy ESWT reduces the expression of pro-inflammatory cytokines and promotes the acquisition of anti-inflammatory cytokines shortly after the application of ESWT [29–31].

Therefore, it can be hypothesized that a one-time ESWT modulates the inflammatory response in several tissues when applied within the acute phase of injury [29, 30, 32]. Also, no neural tissue damage, such as hemorrhage or vacuole formation, was observed in histological analysis after the application of low-energy ESWT to the spinal cord in a spinal cord contusion model in rats [25].

### Extracorporeal shockwave therapy (ESWT) in patients with chronic complete paraplegia (AIS A) at the thoracic level

In 2015, recruitment for a multi-center prospective randomized double-blind clinical study was started including patients suffering from chronic paraplegia (lesion between THII and THX, AIS A = complete central lesion) at least for 1 year after the initial trauma without spontaneous recovery within the last 6 months. In general, a spontaneous recovery of the senso-motoric function is decreasing with the time from injury and is therefore not expected in the study population. In these cases, treatment options are mainly limited to the improvement of the quality of life.

Currently, 34 patients from the intended 50 have been included in the study and recruitment is ongoing until the end of 2020. Therefore, results are not available yet. Until now, no severe side effect or adverse effect occurred to the study participants. Besides the multi-parametric evaluation (neurological, neurophysiological, clinical as well as functional), blood samples have been collected to multiplex protein assessment miRNA analysis.

### Safety and efficacy study: shock wave therapy in patients with ischemic spinal cord injury

[name] and colleagues are working on an ongoing controlled, multi-center, open trial assessing the safety and efficacy of extracorporeal shock wave therapy in patients with ischemic spinal cord injury after aortic surgery or endovascular aortic repair. The study started in July 2017. Until now, five patients have been included in the study and no severe side effect or adverse effect occurred to the study participants.

### Pilot study: the effect of ESWT on peripheral nerve regeneration

Hausner et al. are currently working on a prospective randomized double-blind pilot study in which the authors investigate the effect of ESWT on nerve regeneration after acute traumatic complete dissection of either the median or ulnar nerve and subsequent microsurgical nerve co-adaption. Until now, nine patients have been included in the clinical trial and no severe side effect or adverse effect due to the ESWT occurred to the study participants.

### Risks and benefit

Previous literature reports, that in the planned energy flux density and pulse range, no therapy-associated tissue damage has been observed neither in neural tissue nor in muscle/tendon tissue — even with repetitive application [17, 28, 33, 34].

We consider the application of low-energy ESWT after acute traumatic SCI ethically justifiable because previous studies have shown no adverse events and a positive impact on the central and the peripheral nervous system [12, 17, 23, 25, 34]. The risk to potential benefit ratio is considered in favor of the patient’s benefit.

### Study objectives

#### Primary objective

The primary aim of this study is to investigate whether a greater improvement in motor and sensory function (the AIS grade) can be achieved in patients after spinal trauma (AIS A–D) by applying a single extracorporeal shockwave therapy compared to the control group.

The primary endpoint is the degree of motor and sensory impairment in the American Spinal Injury Association (ASIA) Impairment Scale (AIS) and the International Standards for Neurological Classification of Spinal Cord Injury (ISNCSCI) Score.

The results are compared over the course of time in both groups between the treatment group (one-time low-energy focused ESWT) and the control group (placebo-ESWT).

#### Secondary objective

The secondary objectives include the assessment of changes in spasticity, the ability to walk, urological function, quality of life, and independence in everyday life over time and in comparison between the groups.

## Methods

This is a two-arm three-stage adaptive, prospective, multi-center, randomized, blinded, placebo-controlled clinical trial according to the MPG (Medizinproduktegesetz [Medical Devices Act]) which is designed as a two-arm three-stage adaptive trial.

Fourteen treating hospitals and three rehabilitation centers in Austria and Germany will participate. The allocation of the study groups will occur by means of a block randomization, in order to guarantee the best possible balance between the treatment group, the control group, and the treating hospitals. The study groups are comprised of a treatment group (extracorporeal shock wave therapy by means of electrohydraulic shock wave generation) and a control group (placebo ESWT).

To gain as homogenous groups as possible, a stratified block randomization with a block size of four will be done. The assignment to treatment and placebo group will be made in a ratio of 1:1. For stratification, three different neurological levels of injury will be used:
Cervical injuries: C1–C8Thoracic and lumbar injuries (T1–L1)Peripheral nervous system injuries (cauda equina and conus medullaris syndromes [35]; L2–S5)

Recruitment of patients takes place continually at admission to acute care in one of the 14 participating hospitals (13 in Austria, 1 in Germany). Patients and assessors of study relevant data are blinded to group allocation. The operating room staff and persons involved in the application of the study intervention are not blinded to group allocation and are required to keep it as a secret.

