#### Mode of administration

The extracorporeal shockwave therapy is applied once at the level of the lesion and 5 segments above and below or below the occiput (in lesions higher than C6) and above the sacrum (in lesions lower than T12). The transducer is held in an approximated angle of 45° paravertebral from both sides. In addition, the ESWT is applied to the soles of both feet on the medial side of the plantar surface. In patients who require surgical treatment, the ESWT is applied peri-operatively under extension (about 15 to 20 min) of the general anesthesia (ideally post-operative immediately after skin closure) or within the first 48 h after trauma.

If no surgery is required, the ESWT or placebo application is applied as soon as possible within 48 h from the first recognition of neurological symptoms, both in the intensive care unit after surgery or in the normal ward.

For the application, a sterile film is placed in the treatment area and ultrasound gel is used. The study intervention takes approximately 20 min. In the control group, the same procedure is performed, but without the device emitting extracorporeal shock waves using a dummy head.

The application of the ESWT, as well as placebo ESWT, takes place in a prone position if surgical treatment takes place in a prone position. If the surgery takes place in a supine position, patients are placed in a lateral or prone position post-operatively to apply ESWT.

The treating physician together with the team of medical staff will decide whether an additional 20 min of anesthesia is justifiable for the individual patient. For those who cannot give consent to participate prior to the surgical intervention and are still eligible post-operatively (still within the time frame of 48 h), the medical team has to weigh up if a change of position to prone or lateral position is possible without compromising the individual medical condition.

The follow-up examinations shall be blinded [64]. In order to ensure blinding of the examiner, the entire operating room staff and all persons involved in the application of the study intervention are required to keep the group allocation as a secret.

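### The protocol fixes a published block size of four while device operators are unblinded, and leaves open whether blocks run within hospitals; if they do, some upcoming allocations can be deduced locally.

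*Protocol article*

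**What the plan says.** Protocol article, Methods: to obtain homogeneous groups, "a stratified block randomization with a block size of four will be done", and "The assignment to treatment and placebo group will be made in a ratio of 1:1". Each block therefore holds two active and two placebo assignments. No other block length is mentioned.

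On strata, the same section says "For stratification, three different neurological levels of injury will be used" and lists cervical, thoracic/lumbar, and peripheral (cauda equina and conus). Hospital is not in the list. The analysis section (Hypothesis formulation and testing procedure) likewise uses neurological level as the block variable of the ANOVA. But the paragraph that introduces block randomization gives its purpose as "in order to guarantee the best possible balance between the treatment group, the control group, and the treating hospitals".

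On blinding, Methods says "The operating room staff and persons involved in the application of the study intervention are not blinded to group allocation" and requires these people to keep the allocation secret. Under Placebo, comparator, control patients are treated with a dummy applicator.

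On discretion at the bedside, Mode of administration says "The treating physician together with the team of medical staff will decide whether an additional 20 min of anesthesia is justifiable for the individual patient". Where a patient can consent only after surgery, the medical team also weighs whether repositioning is possible. Under Randomization, the article names a web-based randomization tool.

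**The concern.** A short block of known, fixed length lets anyone who has seen the earlier assignments in that block deduce some of the later ones. A web tool hides the list but does not stop inference from remembered allocations. The secrecy duty protects the blinded assessors; it does not prevent the staff who hold the information from drawing the inference.

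If such a person can also influence whether or when a patient enters, entry could be selective. The trial admits AIS A to D, a wide range of severity, and neither the stratification nor the primary ANOVA uses AIS grade. An imbalance in severity caused by selective entry would be neither prevented nor adjusted for. Blinded assessment and intention-to-treat both act after entry and would not repair it.

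How much can be inferred locally depends on whether blocks run within a hospital, and the article gives two different signals on that.

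**Working it through.** **Inputs from the article.** Block size 4; ratio 1:1; three levels; 14 recruiting hospitals (Methods; the abstract gives 15, which changes little); 82 patients at stage 1 and 246 at most (sample size table).

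**Assumptions, not in the article.** Equal expected accrual across hospitals; local staff remember all past local allocations; for the split by level, either equal thirds or a 50/35/15% mix.

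**One complete block of four.** There are 6 orderings of two A and two B, hence 24 positions.
- The 4th allocation is always known: 6 positions.
- The 3rd is known when the first two match, which has probability 1/3: 2 positions.
- Certain in advance: 8/24 = 33.3%.
- Best guess correct by position: 50%, 66.7%, 66.7%, 100%; mean 17/24 = 70.8%.

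So a cell with k patients has on average (4/3) × floor(k/4) certain allocations, plus 1/3 if k leaves remainder 3 on division by 4.

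**Blocks within hospital.**
- Stage 1: 82/14 ≈ 6 patients each. One full block plus two patients: (4/3)/6 = 22% certain.
- Maximum size: 246/14 ≈ 18 each. Four full blocks plus two patients: (16/3)/18 = 30% certain.
- If hospital sizes vary at random around equal means, the figures are 26% at 82 patients and 31% at 246.

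**Blocks within hospital by level.** 14 × 3 = 42 cells, and 82/42 ≈ 2 patients per cell at stage 1. Averaging the formula above over binomial cell sizes gives about 12% certain with equal thirds and 14% with the 50/35/15 mix. At 246 patients both give 26%.

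**Blocks run centrally by level only.** A hospital sees only its own scattered part of each block. Guessing the arm that is behind in its own history succeeds about 51% of the time (simulated, equal thirds), close to chance. In that case nothing constrains the split within any one hospital, so the stated aim of balancing hospitals is not guaranteed.

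**What varying block lengths would change**, with blocks within hospital and an observer who knows the set of lengths but not which is in use:

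| Block lengths | Certain in advance, 6 / 18 patients per hospital | Simple guess correct at 6 patients |
|---|---|---|
| Fixed 4 | 22% / 30% | 67% |
| 4, 6, 8 | about 1% / 2% | 65% |
| 2, 4, 6 | about 3% / 4% | 69% |

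The simple guess picks the arm that is behind and needs no knowledge of block lengths. Varying lengths therefore remove most certain knowledge but hardly change that guess. A set that includes 2 makes the guess slightly easier at this hospital size.

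**The case against.** The strongest reply is that hospital is not a listed stratum. Both the randomization paragraph and the ANOVA name neurological level alone, and the only contrary evidence is one sentence of purpose. On the listed strata, local predictability is near chance. This stands, and it is why the point is conditional. But that purpose sentence describes something level-only blocks do not deliver, so the text needs settling on either reading.

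A reader might infer that the people who decide on inclusion are the unblinded ones. The documents do not say so. Unblinded status is given to operating room staff and those applying the device; the feasibility judgment is given to the treating physician and medical team; eligibility and consent are placed in a pre-screening (Study procedures). Overlap is plausible, particularly for patients who consent after surgery, but it is not stated. Nor does the article say whether the feasibility judgment comes before randomization. If it comes after, omitting the procedure does not remove the patient, because the analysis keeps patients regardless of whether treatment was delivered as planned (Definition of collective analysis).

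It is also fair that 33% and 71% are properties of any fully observed block of four, and that the trial-specific figures rest on assumed accrual and memory. Finally, the full protocol may contain concealment steps that the article omits, so their absence here is not held against the plan.

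**Conclusion.** The point holds in conditional form and is minor. The article fixes and publishes one block length of four, leaves the operators aware of each allocation, and is inconsistent on whether hospital is part of the blocking.

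- Blocks within hospital: roughly 22–30% of allocations could be known for certain locally, or about 12–14% at stage 1 if blocks are within hospital by level. This rests on the accrual, level-mix and memory assumptions above.
- Blocks central by level: almost no exposure, but the hospital-balance aim is not guaranteed.

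The documents do not support a claim that allocations in this trial are predictable as a matter of fact, or that selective entry has occurred or is likely. What they support is a cheap clarification and, if hospital is a blocking factor, a better block scheme.

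**What to change.** For patients still to be randomized:

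1. State in Methods whether hospital is a blocking factor, and align the sentence on balancing hospitals with the answer.
2. If it is, replace the fixed block of four with randomly varying block lengths not disclosed to sites, for example 4, 6 and 8 rather than a set containing 2. Alternatively, run blocks centrally by level and drop the claim to guarantee balance across hospitals.
3. Have the eligibility and feasibility judgment recorded before the allocation is requested.

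The cost is a short amendment and a change to the randomization set-up. The largest possible arm difference from an unfinished block rises from 2 (half of 4) to 4 (half of 8) per stratum. Varying lengths should not be presented as making guessing impossible: their gain is the removal of nearly all certain knowledge, while the simple guess rate falls only slightly.
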